|                |                                                                                                                                                                                                                                                                                                                                                                                                                                                                                                                                                                                                                                                                                                                                                                                                                               |
|----------------|-------------------------------------------------------------------------------------------------------------------------------------------------------------------------------------------------------------------------------------------------------------------------------------------------------------------------------------------------------------------------------------------------------------------------------------------------------------------------------------------------------------------------------------------------------------------------------------------------------------------------------------------------------------------------------------------------------------------------------------------------------------------------------------------------------------------------------|
| Biometry       | 
Efficacy: Generalised linear mixed model including randomisation strata as covariate and trial site as random intercept, estimation of odds ratio and rate difference with 95% confidence interval (CI).
 
Description of the primary efficacy analysis and population:
 
Full analysis set (FAS): all patients who received the trial medication will be analysed as randomized (intention-to-treat principle)
 
Safety: Frequencies with 95% CI of complication rates and (S)AEs
 
Secondary endpoints: Event rates (incl. 95% CI), chi test, time to cessation of SE by time-to-event methods, (generalized) mixed linear models for longitudinal analyses as well for the other endpoints (e.g. questionnaire scores) similar to the primary endpoint.
 |

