#### **Note!**

Blood sampling and subsequent local lab analysis must not delay start of the patient's treatment.

- Assessment of the GCS,
- perform brief neurological exam: orientation, horizontal extraocular movements, motor drift of both arms and legs, sensation, language
- Obtain the mRS, BI and Home care before admission – if it possible by relatives (see **During 24 hours after T0**)

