## **T60 – 60 minutes after initiation of intervention (+/- 5 minutes)**

- Administer the GCS and perform brief neurological exam: orientation, horizontal extraocular movements, motor drift of both arms and legs, sensation, language
- Obtain a blood sample (EDTA and heparine-plasma and/or serum) for the following parameters:
  - blood count
  - alanine aminotransferase, aspartate aminotransferase, gamma-glutamyl-transferase
  - creatinine, blood urea, glomerular filtration rate
  - sodium
  - level of valproate, level of levetiracetam

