# 8 BIOMETRY

## 8.1 Biometrical Aspects of the Trial Design

### 8.1.1 Measures to Prevent Bias

#### Randomisation

Randomisation in a 1:1 ratio is performed as block randomisation with randomly varying block length stratified by centre.

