#### Efficacy

- Time from initiation of trial intervention to cessation of eSE within 60 minutes
- Neurological status (including vigilance) 60 minutes after initiation of intervention

- Difference of blood levels of VPA and LEV before and 60 minutes after initiation of intervention
- Recurrence of seizures or nonconvulsive/ convulsive SE after initially successful intervention
- For patients who failed the primary endpoint, number of patients in whom SE ceased during 60 minutes after initiation of intervention according to the treating physician
- For NCSE patients who failed the primary endpoint, time to first cessation, as verified by EEG
- Number of patients with SE-associated ventilation until hospital discharge
- Functional outcome at discharge, defined by Barthel Index (BI) and modified Rankin Scale (mRS)

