### 8.5.2 Planned Methods for Analysis

The primary endpoint will be analysed by means of a generalized mixed linear model with binomial link function incorporating randomisation arm as fixed and centers as random effects. Odds ratios are calculated as effect sizes incl. 95% confidence interval (CI) and tested. In secondary analysis, the cessation rates are tested by  $\chi^2$  test. Cessation rates and their difference with 95% CI following Wilson (Newcombe 1998b, 1998a) are calculated.

Other event rates are estimated with 95% CI (Wilson) and possibly are compared by chi-squared test without continuity correction and by mid-p test if expected numbers are too small, respectively. Time-to-cessation is analysed by time-to-event methods (Kaplan-Meier estimates and logrank test).

Latency between start of SE and 1) application of the last benzodiazepines before the start of study medication and 2) start of study medication is analysed by descriptive statistics for CSE and NCSE separately. An adjustment of the primary analysis for these covariates will be considered.

(Generalized) mixed linear models are built for the other endpoints (e.g. questionnaire scores) as well for longitudinal analyses similar to the primary endpoint.

In secondary analysis, the inclusion of the Status Epilepticus Severity Score (STESS, Rosetti et al. 2008) into multiple models for several endpoints is envisaged.

Explorative subgroup analyses are performed for female / male patients, generalized or focal CSE with impaired consciousness/ focal CSE without impaired consciousness / NCSE with coma / NCSE without coma. Although the trial is not powered for these comparisons, the analyses will give valuable new insights on the subtypes of SE and elderly patients.

Due to the short period the patient is in the study, we expect that missing data will be a minor problem. Multiple imputation is envisaged only if a high proportion of questionnaire data is missing. The definition and calculation of derived variables as well as a detailed description of the analysis method is stipulated in the statistical analysis plan. It will be established when data from 10% of the patients are input into the database. This proportion is absolutely necessary to take main properties and relationships of the data into consideration.

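### Protocol 8.5.2 names no baseline term for the 60-minute neurological status endpoint, although GCS is already recorded at screening

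*Protocol*

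**What the plan says.** The Synopsis lists this endpoint among the key secondary ones, and Protocol 8.2.2 repeats it under efficacy: "Neurological status (including vigilance) 60 minutes after initiation of intervention".

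The same scale is measured before and after the infusion. Section 6.2.1 (Screening) includes "Assessment of the GCS" together with a brief neurological exam. At T60, section 6.3 asks staff to "Administer the GCS and perform brief neurological exam". Section 6.3 and the Schedule of Assessments also place GCS at T15 and T30.

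Section 8.5.2 describes the primary model as "incorporating randomisation arm as fixed and centers as random effects". The Synopsis words it as "Generalised linear mixed model including randomisation strata as covariate and trial site as random intercept". Section 8.1.1 specifies "block randomisation with randomly varying block length stratified by centre", so centre is the only stratum and the Synopsis wording adds no patient-level covariate. The sentence on the remaining endpoints is "Generalized) mixed linear models are built for the other endpoints (e.g. questionnaire scores) as well for longitudinal analyses similar to the primary endpoint".

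Section 8.5.2 also envisages the severity score STESS in secondary models for several unnamed endpoints, and it leaves the detailed description of methods to the SAP. Section 8.4 describes the analysis of secondary endpoints as mainly explorative.

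**The concern.** The trial enrols patients from focal convulsive status without impaired consciousness through to nonconvulsive status with coma. Screening GCS can therefore be expected to vary widely and to predict GCS one hour later. Randomisation within centre does not balance it by design. A model built on the primary model's named terms leaves between-patient variation in starting consciousness in the error term. It also leaves any chance difference between the arms in the treatment contrast.

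The primary endpoint offers no comparable baseline, because every patient is in status epilepticus at entry. For the 60-minute neurological status, a pre-infusion value of the same scale is already scheduled. What is at stake is the precision of a key secondary efficacy estimate.

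**Working it through.** **1. The plan's own figure.** Section 8.4 assumes 60% (VPA) and 47% (LEV), two-sided 5% and 80% power. The unpooled normal formula gives (1.96 + 0.842)² × (0.60×0.40 + 0.47×0.53) / 0.13² = 227.15 per arm, or about 454 in total. This matches the stated 454. The pooled version gives 230 per arm, or 460. For drop-out, 454 × 1.05 = 476.7, which matches 477. The sample size is not in question. It gives 227 per arm for the steps below.

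**2. Terms named for the 60-minute endpoint.**

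| Source | Terms named |
|---|---|
| 8.5.2, primary model | arm fixed, centre random |
| Synopsis, Biometry | randomisation strata, site random |
| 8.1.1 | the only stratum is centre |
| 8.5.2, other endpoints | modelled like the primary |
| 8.5.2, STESS | envisaged, secondary analysis, endpoints not named |

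Screening GCS appears in none of these.

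**3. Gain from adjustment.** Let ρ be the correlation of screening with 60-minute GCS. The protocol does not give it, so a range of 0.3 to 0.7 is assumed. With a linear covariate, the variance of the arm contrast is multiplied by 1 − ρ² and the confidence interval width by √(1 − ρ²).

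| ρ | 1 − ρ² | √(1 − ρ²) | CI narrower by |
|---|---|---|---|
| 0.3 | 0.91 | 0.954 | 4.6% |
| 0.5 | 0.75 | 0.866 | 13.4% |
| 0.7 | 0.51 | 0.714 | 28.6% |

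**4. Exposure to chance imbalance.** The standard error of the between-arm difference in mean screening GCS is √(2/227) = 0.094 SD. A difference of 1.96 standard errors is 0.184 SD, and one at least this large in either direction arises in 5% of randomisations. Without adjustment it moves the 60-minute contrast by ρ × 0.184 SD: 0.055 SD at ρ 0.3, 0.092 SD at 0.5 and 0.129 SD at 0.7.

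Given such an imbalance, and no treatment effect, the unadjusted test statistic is approximately normal with mean 1.96ρ and variance 1 − ρ². The chance that it exceeds 1.96 in absolute value is then about 8% (ρ 0.3), 13% (0.5) or 21% (0.7). Averaged over all randomisations it stays at 5%.

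**The case against.** The strongest reply is that the protocol is silent here rather than wrong. Similarity to the primary model may mean a model family and not a closed list of terms, and 8.5.2 passes the detail to the SAP, which is not at hand. The sentence also covers longitudinal analyses, where the GCS series is an obvious candidate. Other parts of the protocol do use earlier values: drug levels are defined as a before-after difference, and 8.2.2 compares mRS and Barthel Index with the premorbid state. STESS models and subgroup analyses by status type, including coma, are foreseen.

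Much of this stands, and it limits the point. A reader might infer that the protocol fixes a model with arm and centre only. It does not say so, and the SAP may add terms. A reader might also infer bias or an inflated error rate. The comparison without baseline is unbiased and keeps its 5% level on average; the figures in step 4 are conditional on an unlucky allocation. A reader might turn the variance factor into a power gain, but 8.4 sets no power target for secondary endpoints and calls power estimation for them not sensible. Finally, a reader might extend the same remedy to every exam item. Motor drift, sensation and language may be untestable during ongoing status epilepticus, so that extension is debatable and is not made here.

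These replies do not remove the point. STESS is tied neither to this endpoint nor to its main model. The longitudinal wording does not say whether the screening value is a covariate, an outcome or absent. Subgroup analyses do not adjust the overall contrast. The general deferral to the SAP leaves unchanged the one model form that the protocol gives. Section 8.5.2 also times the SAP for when data from 10% of patients have been entered, whereas using the baseline of the same scale needs no trial data to justify it.

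**Conclusion.** The point holds as a minor, cost-free improvement. The only model form given for this endpoint carries no baseline term, although a pre-infusion GCS is scheduled, entry consciousness varies widely, and allocation is not stratified by it. The consequence is avoidable imprecision and exposure to chance imbalance. An illustrative size is a confidence interval about 5% to 29% wider than the adjusted interval would allow saving, that is, the adjusted interval is narrower by that share of the unadjusted width for ρ between 0.3 and 0.7.

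This size rests on an assumed ρ, on 227 analysed patients per arm, and on treating GCS as approximately continuous and linear. GCS is a bounded ordinal scale, so the figures are a guide and not a forecast. The endpoint is explorative by the protocol's own description. The primary analysis is untouched.

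**What to change.** Add to 8.5.2, and carry into the SAP:

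- GCS at T60 is analysed with screening GCS as a fixed covariate, alongside arm (fixed) and centre (random).
- In any longitudinal GCS model, T15, T30 and T60 are the outcomes and the screening value is a covariate, not a further outcome.

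The cost is one or two sentences. No patients, visits or measurements are added, and the primary analysis and the sample size stay as they are.

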## 8.6 Statistical Monitoring

The trial conduct will be closely supervised by means of central and statistical monitoring according to ICH E6 (R2). The objectives are

- to detect safety relevant signals as soon as possible,
- to detect relevant protocol violations and to prevent their future occurrence by prompt reaction

Central and statistical monitoring bases on a thorough risk analysis. The main target is to find possible signals of danger for safety of patients and for the success of the trial. Then, actions may be taken timely to amend the trial.

Second, statistical monitoring will deliver data for the meetings of the DMC, too.

Finally, data consistence is proved by checking for extreme / unplausible values as well by cross-checking. This shall ensure a high quality of data evaluation and capturing.

Especially, these topics are important:

- patient accrual
- arm balance
- dropouts and missing values
- patient safety

## 8.7 Interim Analysis

No formal interim analysis for superiority or futility is planned. Even if no treatment difference can be proven, the full sample is desirable to obtain reliable estimates of effect size in the first randomized trial comparing second-line treatment with VPA and LEV in elderly patients.

## 8.8 Final Analysis

When all scheduled patients have finished the trial and all data are inputted the data were finally checked. This may trigger new queries that must be processed. If all queries are answered the database is closed. Then, final analysis may begin.

# 9 ETHICAL, LEGAL AND ADMINISTRATIVE ASPECTS

## 9.1 GCP-Statement

All persons participating in the conduct of the trial (sponsor, authorized representative of the sponsor, investigators, etc.) commit themselves to observe the Declaration of Helsinki of the WMA (in its current version), as well as all pertinent national laws and the ICH guidelines for Good Clinical Practice (GCP) ICH E6(R2) (EMA/CHMP/ICH/135/1995) issued in June 2017.

## 9.2 Initial Submission

### 9.2.1 Submission to the Ethics Committee and Federal Authority

Prior to submitting the trial related documents to the leading (and involved) ethics committee(s) and the responsible federal authority, the sponsor must enter the trial into the European database for clinical trials (EudraCT).

Afterwards, the protocol and all other associated documents according to GCP-V §7 will be submitted to the leading ethics committee for approval. Parallel to the submission to the leading ethics committee (EC), each participating EC is informed of the submission and also receives a copy of the documents including those of the trial sites, which they have to approve. At the same time the study documents will be submitted to the responsible federal authority (BfArM) according to the requirements of GCP-V §7.

The trial can start only after obtaining a positive review by the leading ethics committee and approval from the responsible federal authority. The written approval of the EC must be filed

in the trial master file (TMF). Additionally, every participating centre must receive a copy of these documents to be filed in the investigator site file (ISF).

### 9.3 Protocol Amendments

Changes made to the protocol that was appraised positively by the ethics committee and approved by the responsible federal authority must be positively reappraised and approved if the changes

- are such that they may affect the subjects' safety
- fundamental changes to the therapeutic procedures
- updates to the SmPC that may have an impact on the assessment of adverse events, including the definition of possible SUSARs
- result in further data collection that necessitates changes to the patient information and/or informed consent form,
- affect the interpretation of the scientific documents upon which the trial is based or the significance of the results of the trial,
- significantly affect the leadership or conduct of the trial, or
- concern the quality or the innocuousness of the investigational drug

Changes to the protocol may only be performed by the sponsor, the authorised representative or the coordinating investigator in co-operation with the biometrician.

After approval of the trial changes, all participating trial sites have to be informed about the changes in writing and supplied with potentially changed documents.

The whole process has to be documented in the Trial Master File (TMF).

## 10 DOCUMENTATION

### 10.1 General information and Access Rights

In the context of a database for electronic data capture only, the Case Report Form (CRF) will be designed by the ZKS Leipzig in cooperation with the Coordinating Investigator and provided as electronic form (eCRF). In order to facilitate the documentation as per protocol in case of malfunction of the electronic system or any of its components, a paper version of the CRF (interim CRF) will be provided in the ISF (investigator site file). The data on this paper version will be transferred to the eCRF as soon as the electronic system is available again.

Special CRF forms will be provided as paper CRF:

- **SAE-forms**, because these have to be sent to the ZKS Leipzig in a printable version for submission to the relevant authorities

An eCRF will be provided for each patient. The patient will be identified as per patient-ID only. The eCRF must be completed shortly after each trial visit according to ICH Guideline E6 chapter 4.9.1 and to enable central monitoring of the trial data.

Access to the data base will be limited to authorised staff only. Authorisation is granted by the site's investigator using the trial specific staff signature and delegation log. Based on the staff signature and delegation log access to the eCRF will be granted by the responsible staff at the ZKS Leipzig.

Authorised staff members on site will be able to enter and update data as well as finalise data by electronic signature during the conduct of the trial according to a trial specific concept for documentation. This concept is based on the internal Standard Operating Procedures implemented by the ZKS Leipzig and follows the ICH Guideline E6. All entries and data changes will be tracked automatically including date, time and person who entered/changed information (audit trail). Major correction(s) or major missing data have to be explained.

## 10.2 Patient File and Source Data

All information required by the protocol and therefor collected during the clinical trial must be recorded by the Investigator or an authorised member of the trial team as source data in the source documentation for the trial (e.g. patient file).

Source data according to ICH Guideline E6 are defined as any information in original records and/or certified copies of original records of clinical findings, observations, or other activities in a clinical trial necessary for the reconstruction and evaluation of the trial. Source data are contained in source documents.

The Source Data Agreement is defining source data and their location for respective CRF entries. It will be filled in at the initiation visit, signed by the investigator or deputy investigator and filed in the trial master file.

In order to confirm the completeness, accuracy and consistency of the data with the data in the source documents the investigator or deputy investigator has to electronically sign each patient's CRF after his/her individual end of trial participation.

## 10.3 Data Management

For creation of the trial database the EDC tool secuTrial®, developed and distributed by interActive Systems GmbH (iAS), will be used. The database will be validated according to the Standard Operating Procedures (SOPs) of the ZKS Leipzig prior to data capture.

The information entered into the eCRF by the investigator or an authorised member of the trial team is systematically checked for completeness, consistency and plausibility by routines implemented in CDMS such that discrepancies can be dealt with at data entry. Errors and Warnings are listed in a validation report and can be resolved at any time during entry process. On completion of the data entry the site staff flags the eCRF-pages as 'data entry completed' (DEC).

During on-site monitoring or central/statistical monitoring, the monitor or the data manager at the ZKS Leipzig may create a manual query for discrepancies that are identified after DEC. All eCRF-pages with queries are marked in the system and a report with all queries listed is available. The site staff is responsible for data correction and can resolve queries directly in the eCRF-page.

The ZKS Leipzig will supervise and support the solution of queries and will close all correctly resolved queries. In case a query cannot be solved, the data management staff may close the query in agreement with the trial biometrician.

In case of self evident corrections by datamanagement staff, a list of self evident corrections or data entry conventions (e.g. for data entry of paper-based life questionnaires) will be available and authorised by the coordinating investigator or the responsible biometrician of the clinical trial. Each trial site will receive a list of performed SECs at the end of the trial.

During the whole course of the trial, a backup of the data is made on a daily basis according to the backup policies of the ZKS Leipzig. Unauthorised access to patient data is prevented by the access concept of the trial database, which is based on a strict hierarchy and role concept.

Any change of data (e.g. when data is changed in the database during query management) is recorded automatically via audit trail within the database.

At the end of the trial, once the database has been declared complete and accurate, the database will be locked. Thereafter, any changes to the database are possible only by joint written agreement between sponsor/sponsors authorised representative/coordinating investigator, biometrician and data manager.

A pseudonymised evaluation and anonymised publication of the data is ensured.

